#### MRI Assessment Battery

Participants are scanned with a 32-channel head coil on a 3T Prisma Siemens MR scanner at the Clinical Imaging Research Centre (CIRC), located at the National University of Singapore. Both structural and functional data are acquired during the MRI scan, with the full protocol detailed in Table 2.

**Table 2 T2:** MRI scan timeline (sequences, durations, purposes).

	Sequence	Purpose	Time (min)
1	Localizer	For field-of-view positioning	0:14
2	3D MPRAGE	High-resolution anatomical scan	5:01
3	BOLD_Resting	Resting state functional connectivity	9:01
4	BOLD_FNPA	Brain activations under FNPA task	7:36
5	BOLD_SIN	Brain activations under singing task	2:36
6	BOLD_auditory localizer	Localization of auditory cortex	3:06
7	Gre field map	For distortion correction	1:07
8	Ep2d_diff (DTI)	White matter integrity	9:06
9	T2_SWI	For detection of micro-bleeds	4:54
10	T2_TSE_ FLAIR	To detect and characterize structural lesions	4:28
11	BOLD_TUNE	Brain activations under musical memory task	3:06
		TOTAL	50:15

The structural scans will allow the tracking of changes in brain volumes and rates of atrophy over time for the whole brain, hippocampus and temporal horn. In addition, changes in white matter integrity over time will be examined through fractional anisotropy, mean diffusivity, and radial diffusivity. The number of white matter lesions and cerebral micro-bleeds will also be recorded. If the choral-singing intervention does indeed confer greater protection from cognitive decline than general health education, a lower rate of structural change should be observed in participants assigned to the choral singing group as opposed to the control group.

Besides structural data, both task-based and functional data are collected as well. The resting state functional data will be analyzed for the strength of intra-network connectivity in large scale networks like the default mode network. The network connectivity of the choral singing group should be more coherent than that of the control group if the choral-singing intervention confers greater protection from cognitive decline than general health education. The task-based functional data are primarily exploratory in nature and are meant to see if participants in the choral singing group are able to fare better in tasks involving auditory stimuli. The tasks are described below.

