MRI images obtained from baseline and follow-up visits will be used to track relevant features such as hippocampal, whole-brain, total cerebral volume and annualized rate of atrophy; total ventricular volume, temporal horn volume; white matter volume and shape; fractional anisotropy and mean diffusivity and radial diffusivity; and the number of white matter lesions and cerebral micro-bleeds. Software such as FreeSurfer and BrainVoyager will be used in image processing and analysis. Functional connectivity analysis will be conducted using group ICA to track changes in networks such as the default mode network and the social brain network. As the face-name paired associates and melodic memory tasks are expected to involve episodic memory, the hippocampus is an *a priori* area of interest. Hemodynamic response function (HRF) time-locked to the presentation of stimuli will be extracted and analyzed.

For all data sets, a linear mixed-effects model will be used to analyze changes in mean responses over time for each group and the interaction term between group allocation and the time variable. A significant group × time interaction will indicate an effect of the choral singing intervention, following which appropriate *post hoc* tests can be done.

Intention-to-treat and per protocol analyses will be conducted. Compliance is monitored. Sensitivity analysis will be conducted by excluding subjects whose compliance (attendance) rate is below a specific cutoff point.

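### The only white-matter lesion measure named is a count, which can stay flat or fall while lesion burden rises; lesion volume would be a better variable for this mechanistic outcome

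*Protocol article*

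**What the plan says.** The lesion measure is stated in two places in the protocol article, both times as a number. Under MRI Assessment Battery: "The number of white matter lesions and cerebral micro-bleeds will also be recorded". Under Methods of Analysis, the features to be followed include "the number of white matter lesions and cerebral micro-bleeds", taken from "MRI images obtained from baseline and follow-up visits". Table 1 puts brain MRI at baseline, 1 year and 2 years.

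The other structural features in Methods of Analysis are mostly volumes, atrophy rates and diffusion measures. For white matter they are "white matter volume and shape; fractional anisotropy and mean diffusivity and radial diffusivity". Neither section names lesion volume, a burden grade or a rule for lesions that join.

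Two statements govern how a result will be read. MRI Assessment Battery says that if singing protects better than health education, "a lower rate of structural change should be observed in participants assigned to the choral singing group as opposed to the control group". Methods of Analysis applies a linear mixed-effects model to all data sets and takes a significant interaction of group with time as evidence of an intervention effect.

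Table 2 includes a 3D MPRAGE (5:01 min) and a T2 FLAIR sequence (4:28 min). The purpose given for the FLAIR is "To detect and characterize structural lesions".

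**The concern.** White-matter lesions and micro-bleeds share one metric although they behave differently under it. A micro-bleed is a discrete focus, so a count is a natural summary. A white-matter lesion has extent. It can enlarge without changing the count, and two neighbours that enlarge until they join become one. The count therefore need not rise when the burden rises.

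This matters because of the reading rule. Less structural change is taken as protection, so a flat or falling count would be read favourably. A participant whose lesions have grown and joined would contribute apparent stability or improvement to the model. At stake is the interpretation of one item in the mechanistic imaging battery.

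**Working it through.** The document gives no lesion figure to reproduce. The check has two parts: what the text fixes, and whether a count can move against burden.

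**Text.** Both sections say number. The analysis section puts every data set into the mixed model, so the count is a modelled response. White matter volume in the feature list reads most naturally as tissue volume, not lesion volume. Fractional anisotropy, mean diffusivity and radial diffusivity describe white-matter integrity. They may register worsening, but they do not measure lesion load.

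**Geometry.** The sizes and spacings below are assumptions chosen for illustration; none comes from the document. Take two equal spherical lesions of radius r with centres a distance d apart.

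- Volume of one sphere: V = (4/3)πr³.
- If d ≥ 2r, the lesions are separate: count 2, total volume 2V.
- If d < 2r, they overlap: count 1, total volume 2V − 2·πh²(3r − h)/3, where h = r − d/2.

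Start: diameter 6 mm (r = 3), so V = 113.1 mm³. The count is 2 and the total is 226 mm³ at each spacing used.

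Worked case, d = 8 mm, growth to 9 mm (r = 4.5):

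- 2V = 2 × 381.7 = 763.4 mm³.
- h = 4.5 − 4 = 0.5.
- Each cap is π × 0.25 × (13.5 − 0.5)/3 = 3.40 mm³, so two caps are 6.8 mm³.
- The total is 763.4 − 6.8 = 756.6 mm³. The change is 756.6/226.2 − 1 = +234%, while the count goes from 2 to 1.

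The full grid:

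| Spacing (mm) | Final diameter (mm) | Count | Final volume (mm³) | Volume change |
|---|---|---|---|---|
| 7 | 8.2 | 2 → 1 | 569 | +151% |
| 7 | 9 | 2 → 1 | 737 | +226% |
| 7 | 11 | 2 → 1 | 1272 | +463% |
| 8 | 8.2 | 2 → 1 | 577 | +155% |
| 8 | 9 | 2 → 1 | 757 | +234% |
| 8 | 11 | 2 → 1 | 1323 | +485% |
| 10 | 8.2 | 2 → 2 | 577 | +155% |
| 10 | 9 | 2 → 2 | 763 | +238% |
| 10 | 11 | 2 → 1 | 1385 | +513% |

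In seven of nine cases the count halves while volume rises by 151% to 513%. In the other two the count does not move while volume rises by 155% and 238%.

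**The other direction.** The grid has growth but no new lesions. If one new 6 mm lesion appears and nothing else changes, the count goes from 2 to 3 and volume from 226 to 339 mm³ (3 × 113.1), a rise of 50%. Count and burden then move together. The net behaviour of the count depends on the mix of new lesions, growth and merging, and the document says nothing about that mix. The seven-of-nine tally reflects the sizes chosen and is not an estimate of frequency.

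**The case against.** The strongest reply is that this is a condensed article with an open list. The feature list is introduced by way of example ("will be used to track relevant features such as hippocampal, whole-brain, total cerebral volume and annualized rate of atrophy"), and the stated FLAIR purpose is wider than counting. Lesion volume is therefore unnamed, not excluded, and segmentation detail commonly sits in a fuller protocol. This stands as far as it goes: a reader might infer that nothing planned captures lesion load, and the text does not support that. It does not remove the point, because the metric the article does state, twice, is the weak one.

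A second reply is that nothing in the article shows how lesions evolve at this age. This also stands. It would be tempting to say that growth and joining dominate after age 60, but the article gives no basis for that. The argument needs only that growth and merging can occur.

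A third reply concerns the comparison between arms. A reader might infer from "a lower rate of structural change should be observed in participants assigned to the choral singing group" that the arm with more progression would look better, reversing the sign. That would require merging to outweigh new lesions, and to do so by more in the worsening arm. No figure in the article supports it. Nor does the text set out a vascular mechanism that would be overturned. It speaks of neuroplasticity, immune function, inflammation and oxidative damage, and the structural hypothesis covers several volumes and diffusion measures besides the count.

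Finally, the stakes are limited. The lesion count is neither the primary outcome nor among the listed secondary outcomes.

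**Conclusion.** The point holds in a limited form. The article names only a number as its lesion measure and models it over time by arm. That number is not a monotone measure of lesion burden. In an individual participant, worsening can appear as stability or improvement. This follows from geometry alone.

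The size of the effect at trial level cannot be given, because the rates of new, growing and merging lesions over 2 years are not stated. What can be claimed is loss of sensitivity and possible bias in one mechanistic measure. A reversed treatment contrast is not shown. The primary composite cognitive result is unaffected, the micro-bleed count is sound on this argument, and the diffusion measures may pick up some of what the lesion count misses. Importance is low to moderate. The change is worth making because it replaces a stated metric with a better one at small cost.

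**What to change.** In Methods of Analysis and MRI Assessment Battery, name total white-matter lesion volume as the lesion variable in the group-by-time mixed model. Segment it from the FLAIR and MPRAGE scans, scale it to intracranial volume, and log-transform it if skewed. Keep the count for micro-bleeds. Report the lesion count descriptively only.

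Set this definition before lesion data are compared between arms. The Progress section describes data processing as ongoing and places final collection in February 2020, so there is room to do so before the final analysis.

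The cost is segmentation work and quality checks on scans already planned, with no added scan or visit. Feasibility is inferred from the sequences in Table 2 and from the plan to use image-processing software. The article does not give FLAIR resolution or say that the named software segments lesions, so the imaging team should confirm both.

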## Methods of Analysis

CCTS at each follow-up visit, absolute changes from baseline and percentage changes from baseline during the intervention period will be compared between the two arms using Student’s *t*-test and repeated-measures analysis of variance (ANOVA). Following this, a linear mixed-effects model will be conducted to examine the main effect of time and group allocation, and the interaction between time and group allocation, adjusting for potential confounders where necessary. Fisher’s exact tests will be used to compare the difference in dichotomous outcome measures such as cognitive decline, defined as the one or more points in MMSE score, between the two arms. Multiple logistic regressions with adjustment for important baseline characteristics will be conducted in the event of important baseline non-comparability. Statistical analysis will be conducted using SPSS, Stata or R. Interim analysis will be conducted for the first group of participants using data collected at 6 months, 12 months and 24 months, respectively.

The statistical analysis for DNA methylation will be performed using a modified version of the CPACOR pipeline to eliminate potential confounders such as bisulfite conversion, batch effect, and white blood cell composition (Lehne et al., 2015). Marker intensities will be normalized by quantile normalization. We will use the epigenome-wide methylation scores to impute white blood cell subsets using the Houseman method (Houseman et al., 2014). A principal components analysis will also be performed to quantify latent structure in the data, including batch effects. Single-marker tests using logistic regression will be used to examine the association of each autosomal CpG site with condition (choral singing/control), adjusted for age and sex. We will also calculate the methylation age using the 353 CpG sites previously identified (Horvath, 2013). Principal components from intensity values of Infinium control probes, which accounts for various technical parameters such as bisulfite conversion batch, will also be included as covariates in the regression models. Finally, the association results will be adjusted for genomic control inflation factor.

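### The group × time rule is written for all data sets, but for the listed annualized atrophy rate it does not test the stated hypothesis of a lower rate (minor; MRI measure only)

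*Protocol article*

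**What the plan says.** The relevant text is in three places of the protocol article.

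- **Methods of Analysis, MRI features.** The features to be tracked include "hippocampal, whole-brain, total cerebral volume and annualized rate of atrophy". A rate is thus listed alongside levels, with no separate analysis for it.
- **Methods of Analysis, general rule.** The next paragraph reads "For all data sets, a linear mixed-effects model will be used to analyze changes in mean responses over time for each group", together with the interaction term, and concludes: "A significant group × time interaction will indicate an effect of the choral singing intervention". Post hoc tests follow a significant result. No exception is made for outcomes that are themselves rates.
- **MRI Assessment Battery.** If singing protects, "a lower rate of structural change should be observed in participants assigned to the choral singing group as opposed to the control group".

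Table 1 schedules brain MRI at baseline, 1 year and 2 years.

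**The concern.** Group × time is the right contrast when the response is a level, such as a volume, and baseline is one of the time points. The arms then start equal on average because of randomization, and any treatment effect appears as diverging trajectories.

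A rate of atrophy has already been differenced over time. If singing lowers the rate by the same amount in both years, the two arms' rates run parallel. The treatment effect is the gap between them, which is the group main effect. Group × time on rates asks a different question: whether that gap differs between year 1 and year 2.

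Applied literally to the rate, the rule would therefore show no effect under the very pattern that the MRI section predicts. It would respond instead to a gap that appears in one year and not the other. The same scans could then yield an effect on volume and none on rate, and the text does not say which result governs.

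**Working it through.** **Inputs from the article.** MRI at 0, 1 and 2 years (Table 1). Total N = 360 (Participants) with 1:1 allocation (Randomization), so 180 per arm. The article gives no alpha, power, effect size, SD or number of participants scanned, so there is no stated figure to reproduce.

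**Assumptions.** Two-sided alpha 0.05. All 360 participants scanned, with complete data. In baseline SD units: between-person slope SD 0.2, residual SD 0.3, and a constant yearly benefit b of 0.05 to 0.15.

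**Step 1: what the interaction tests.** Write y0, y1, y2 for a person's volumes. The interval rates are r1 = y1 − y0 and r2 = y2 − y1. With two occasions and complete data, group × time on the rates is the arm difference in

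r2 − r1 = y2 − 2·y1 + y0.

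A constant benefit b shifts r1 and r2 equally, so the expected arm difference is b − b = 0. Power then equals alpha, whatever N, the SDs or b may be.

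**Step 2: other ways to form the rate.**

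- Cumulative change divided by years gives (y2 − y0)/2 − (y1 − y0) = (y2 − 2·y1 + y0)/2. This is half the same contrast, so the test is identical.
- One 2-year rate per person, (y2 − y0)/2, leaves one observation each. No group × time term exists.

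**Step 3: the contrast that matches the hypothesis.** The mean rate is (r1 + r2)/2 = (y2 − y0)/2.

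- SD = √(0.2² + 2 × 0.3²/4) = √0.085 = 0.292
- SE of the arm difference = 0.292 × √(2/180) = 0.0307
- Power ≈ Φ(b/0.0307 − 1.96)

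**Step 4: group × linear time on raw volumes.** The contrast is y2 − y0, with expected arm difference 2b and SD √(0.16 + 0.18) = 0.583. Both are exactly twice the values in step 3, so the power is the same.

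| Yearly benefit b (SD) | Group × time on rates | Group effect on mean rate | Group × linear time on volumes |
|---|---|---|---|
| 0.05 | 5% | 37% | 37% |
| 0.08 | 5% | 74% | 74% |
| 0.10 | 5% | 90% | 90% |
| 0.15 | 5% | 99.8% | 99.8% |

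**Step 5: simulation check.** In 4,000 trials per setting, for b = 0.05, 0.10 and 0.15, the interaction on rates rejected 4.5% to 5.7% of the time with 180 per arm. With 144 per arm (20% loss) it rejected 4.6% to 5.0%. The group effect on the mean rate rejected 35%, 90% and 99.9% with 180 per arm, and 31%, 83% and 99% with 144. If time is categorical in the volume model (a 2-df test), power with 180 per arm is 27%, 84% and 99%: somewhat lower, but far above 5%.

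**The case against.** **The natural reading is harmless.** The rule speaks of changes in mean responses over time, and on volumes the fitted slope is itself the annual rate of atrophy. Group × linear time is then the hypothesised difference, and no sentence says that two rates per person will be entered as the response. This is a fair reading, and step 4 shows that it works at full power. It stands as a limit on the harm. It does not repair the text, because the rate is listed as a feature in its own right and the rule admits no exception.

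**The rule is one-directional.** It says what a significant interaction means, not what a non-significant one means. That is true, but no other criterion for an effect is named for the MRI data.

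**Detail belongs to the SAP.** How each derived MRI feature is modelled can properly be left there. The point is not a missing detail: the article states a rule and its scope, and the rule is wrong for one outcome within that scope.

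**A stronger reading.** A reader might infer that the primary outcome suffers the same fault, since the plan says "CCTS at each follow-up visit, absolute changes from baseline and percentage changes from baseline during the intervention period will be compared between the two arms". The document does not support that:

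- Those comparisons use t-tests and repeated-measures ANOVA, and a t-test on change is already the group contrast.
- The mixed model that follows includes a group main effect and is not said to be fitted to change scores.
- Change from baseline is cumulative, so a benefit growing by b per year does produce an interaction: 17% to 86% power for b = 0.05 to 0.15 under the same assumptions. Only a gap complete by year 1 and flat afterwards gives about 5%, and the other planned comparisons would pick that up.

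**Conclusion.** The point holds in a narrow form and is minor. For the annualized rate of atrophy, the stated rule does not test the stated hypothesis: a constant slowing is detected only at the alpha level, and with one rate per person the rule cannot be used.

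The 5% figure rests only on the assumed two-sided alpha of 0.05. The 37% to 99.8% for the correct contrast rests on assumed effect sizes and SDs, and on all 360 participants being scanned; it shows a range and is not a prediction for this trial.

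A reader might go further and conclude that the trial would miss a real slowing of atrophy. That does not follow, because the volumes are in the plan under the same rule and carry the same signal. The impact is confined to one mechanistic MRI measure. The composite cognitive score, and other outcomes analysed as levels with baseline in the model, are not affected.

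**What to change.** In Methods of Analysis, limit the group × time criterion to responses analysed as levels with baseline as a time point. Add that for the annualized rate of atrophy, and for any other outcome expressed as a rate, the treatment effect is the between-arm difference in mean rate or, equivalently, group × linear time on the raw volumes.

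This costs one or two sentences, with no new data, visits or participants.

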## Progress

Starting from July 2015, 404 community-living seniors were invited to the screening. Of these, 197 participated and 93 were recruited. The target of identifying and randomizing the first group of participants was achieved in October 2015. The intervention was initialized on schedule with the choral singing intervention starting on 29 October 2015 and the control intervention starting on 4 November 2015. More participants will be recruited through 2017 and 2018 until the target of 360 is met. Final data collection is expected to take place in February 2020 (see Figure 2 for participant flowchart; Schulz et al., 2010). Baseline measurements, MRI scans, bio-sampling and follow-up measurements at 6 months and 1 year after the start of the intervention have been collected for the first batch of participants. Electronic data entry and processing are ongoing. The baseline characteristics of the first group of participants are summarized in Table 3.

**Figure 2 F2:**
[figure not shown]
Flow diagram of participants’ progression through phases of RCT as of May 2017. Adapted from Schulz et al. (2010). *Other reasons: four with hearing impairment, one with visual impairment, one with advanced cancer, two participating in other studies, two received recent neuropsychological assessment, one relocated outside the defined recruitment area.

**Table 3 T3:** Baseline characteristics of the first 93 randomized trial participants.

Variable	Choral singing (*n* = 47)	Controls (*n* = 46)	*p*-value
Age (year), mean (SD)	70.98 (0.835)	69.39 (0.779)	0.168
Women, n (%)	76.6	80.4	0.652
Education, n (%)			0.235
No formal schooling	21.3	8.7	
Primary and below	53.2	63.1	
Secondary and above	25.5	28.2	
Marital status			0.925
Married	55.3	54.3	
Divorced/Widowed/Single	44.7	45.7	
Living alone, n (%)	14.9	15.2	0.965
SMCC total score, mean (SD)	39.32 (0.964)	38.41 (0.642)	0.438
MMSE total score, median (IQR)	29 (27–30)	29 (27–30)	0.720
MoCA total score, median (IQR)	26 (24–28)	26 (25–29)	0.766
GDS total score, median (IQR)	2 (0–3)	1 (0–2.25)	0.246
GAI total score, median (IQR)	0 (0–4)	0 (0–1)	0.122
PSS total score, mean (SD)	15.53 (0.633)	14.91 (0.493)	0.444
GoldMSI score, mean (SD)	58.94 (1.71)	55.93 (1.79)	0.229

*Baseline comparability of the randomized groups was assessed using independent samples Student’s t-tests for continuous variables meeting the assumption of normality and Mann-Whitney tests for variables violating the normal distribution assumption. Chi-square tests and Fisher’s exact test were run for dichotomous variables. No significant differences between randomized groups were found*.

